## Abstract

COVID-19 can cause important sequels in the respiratory system and frequently presents loss of strength, dyspnea, polyneuropathies and multi-organic affectation. Physiotherapy interventions acquire a fundamental role in the recovery of the functions and the quality of life. Regarding the recovery phases after hospital discharge, the current evidence available is very preliminary. Telerehabilitation is presented as a promising complementary treatment method to standard physiotherapy. The main objective of this research is to evaluate the effectiveness of a personalized telerehabilitation intervention after discharge from hospital for the improvement of functional capacity and quality of life compared to a program of health education and/or care in a rehabilitation center. As secondary objectives, to identify the satisfaction and perception of patients with the telerehabilitation intervention and the presence of barriers to its implementation, as well as to evaluate the cost-effectiveness from the perspective of the health system. This study protocol will be carried out through a single blind multicenter randomized clinical trial in the south of Spain. We hypothesize that the implementation of a telerehabilitation program presents results not inferior to those obtained with the current standard intervention. If the hypothesis is confirmed, it would be an opportunity to define new policies and interventions to address this disease and its consequences. Trial registration NCT04742946.

## 1. Introduction

Severe acute respiratory syndrome coronavirus 2 (SARS-CoV-2) causes coronavirus disease 2019 (COVID-19). On 11 March 2020, COVID-19 was categorized as a pandemic and its outbreak was declared a public health emergency of international concern [1,2,3]. Current reports estimate that 80% of cases are asymptomatic or mild; 15% of cases are severe (infection requiring oxygen supply); and 5% are critical patients requiring ventilation and life support [2,4,5,6]. The average time from symptom onset to recovery is two weeks when the illness is mild; and three to six weeks when it is severe or critical. It should be noted that between 75–80% of hospitalized patients will be admitted to hospital for a long period of time (±21 days) [7].

COVID-19 can cause important sequelae in the patient after the virus has been overcome, one of the main ones being respiratory system involvement by bilateral pneumonia. Loss of strength, dyspnea, polyneuropathy and multiorgan involvement (liver, myocarditis and even brain damage) are also common [5,8,9]. Consequently, physiotherapy is playing a vital role in this pandemic and will be fundamental in improving the health of many of the patients. Recent studies already indicated a loss of pulmonary capacity of between 20% and 30% [10]. Therefore, it is a multiorgan disease with a wide and heterogeneous range of sequelae, the extent of which is not yet known [11].

### 1.1. Physiotherapy in Patients with COVID-19

Physiotherapy has a very important role in the functional recovery of patients with COVID-19, both at the respiratory and motor levels in their different phases of evolution [12]. International studies and expert consensus begin to draw the roadmap for physiotherapists in the different stages of coronavirus both for patients in intensive care units and during their hospital stay on the ward [13], defining the available evidence on each modality of intervention [14]. An international group of experts in cardiorespiratory physiotherapy met to urgently develop a clinical practice guideline in the approach of physiotherapy to COVID-19. The group focused mainly on case management interventions in the acute hospital phase where rehabilitation intervention is essential to limit severity and promote early functional recovery [14]. Research has pointed out the indispensability of providing physiotherapy services including weekends and holidays [15].

With respect to the recovery phases, discharge from hospital and subsequent confinement for up to 14 days, according to health recommendations, the data currently available are preliminary [16]. In this recovery and discharge phase, two types of patients are differentiated:

For patients with a mild-moderate respiratory process, the short-term goal will be to gradually restore physical and psychological condition with a series of aerobic exercise guidelines to restore pre-hospital exercise capacity [16].

For patients with a severe/critical process, the evidence indicates that at the time of discharge patients with COVID-19 may experience physical deconditioning, dyspnea secondary to exercise and muscular atrophy among other sequelae [17,18]. In these patients with a severe/critical process, the main physiotherapy interventions will be based on: patient education, aerobic exercise, strength and training exercises, secretion drainage and ventilatory techniques, if the patient’s clinical manifestations so require, exercises aimed at strengthening the peripheral muscles, changes in position and remaining active whenever possible and when the situation of clinical stability permits [17,18].

### 1.2. Telerehabilitation

This term is used to describe the provision of rehabilitation services at a distance, using communication technologies [19]. An expanded definition includes applications such as consultation, home care, monitoring, therapy and patient self-care that are provided in various locations including the home, community, health services and the workplace [20,21].

In addition to traditional physical therapy, studies based on telerehabilitation programs have published results of effectiveness, validity, non-interference and important advantages in some neurological, cognitive, musculoskeletal and respiratory disorders, providing an opportunity to define new policies and social interventions [22]. There is a growing interest in the use of technology for respiratory health interventions [23]. Telerehabilitation offers an alternative approach that can better meet the needs of patients with airway and lung impairments especially in terms of ease of access and elimination of travel [24] and in the case of COVID-19 by limiting their possible transmission by avoiding human-to-human contact.

Currently, health systems are immersed in a continuous process of innovation to improve the effectiveness of health services [25,26]. Telerehabilitation is presented as a promising complementary treatment method to standard physiotherapy, providing physiotherapy support at any time and in any place, both in the health field, community environment, and the home in several pathologies [27,28]. It has also been stated that the high viability and acceptability of this technology can be satisfactory to obtain an improvement in the quality of life of patients [29].

Although it is still too early to state with a high level of evidence the consequences of COVID-19 on functional capacity, the need to implement pulmonary rehabilitation programs in these patients is based in evidences in similar pathophysiology [30,31,32].

The main objective of this research is to evaluate the effectiveness of a personalized telerehabilitation intervention in patients diagnosed with COVID-19 after discharge from hospital for the improvement of functional capacity and quality of life compared to a program of health education and/or care in a rehabilitation center. As secondary objectives, to identify the satisfaction and perception of patients with the telerehabilitation intervention and the presence of barriers to its implementation, as well as to evaluate the cost-effectiveness from the perspective of the health system. The hypothesis of this research is that the implementation of a telerehabilitation (TR) program in patients with COVID-19 presents no inferior results in the improvement of functional capacity and quality of life compared to those obtained with a health education program and/or care in a rehabilitation center.

## 2. Material and Methods

This research is carried out by means of a single blind multicenter randomized clinical trial in patients residing in Andalucía (south of Spain) with a COVID-19 diagnosis who have been discharged from hospital. This research uses the guidelines on Standards for Quality Improvement and Excellence in Reporting (SQUIRE) [33] and will be carried out in accordance with CONSORT (Consolidated Standards of Reporting Trials) criteria [34]. A Standard Protocol Items Recommendations for Interventional Trials (SPIRIT) checklist is provided as Additional file 1, and the flow diagram for the study protocols is included as Figure 1.

### 2.1. Patients

The study includes adults diagnosed with COVID-19 with mild-moderate and severe-critical respiratory processes who have been treated in hospitals in (south of Spain) and who have been discharged from hospital. The fundamental ethical precepts according to the Helsinki Declaration [35] and Law 14/2007 of 3 July on Biomedical Research will be respected, guaranteeing the protection and confidentiality of data. This trial has the approval of the Andalucía Ethics Committee with HIP version 281020. Patients in the study are required to read and approve the consent form.

Patients must reside or stay in the Andalucía (south of Spain) during the intervention phase, have computer technology with an Internet connection at home (including one of the following devices: desktop personal computer, laptop, tablet or smartphone), and be able to access e-mail or WhatsApp frequently and reliably. Patients who are not in full cognitive capacity to use new technology tools will be excluded.

For the development of this research, an intentional non-probabilistic type of sampling will be used for the convenience of the study, due to the characteristics of the subjects.

A sample size of (*n* = 237) with a proportional distribution for each arm of the study (group TR = 118 + control group = 117) with an expected proportion of losses (R = 15%) and a confidence index IC = 95% was used.

Patients are recruited from hospitals rehabilitation and physiotherapy departments. Strategies to achieve an adequate inclusion of participants that reach the target size of the sample include the multidisciplinary collaboration of south of Spain hospitals, heads of rehabilitation services and Physiotherapist teams. The collaborators will be informed about the characteristics of the study in personal interviews and presentation of the project. Patient recruitment seeks to ensure socio-demographic diversity in relation to social origin, gender, ethnicity and education adapted to the particularities of the reference population in Andalucía and prior information on compliance with data protection laws. We will try to make sure that the sample data are homogeneous at the beginning of the study, trying not to have significant differences in demographic, medical and other variables.

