#### Statistical Analysis

The results of the research will be presented as a summary of the outcome measures, together with the estimated effect size and its precision. The statistical analysis will be performed according to the intention-to-treat principle using SPSS software.

The filiation data of the participating subjects will be presented by means of frequency tables and histograms. A descriptive statistical analysis of the different variables will be carried out with frequency tables, bars and sectors in order to have as much information as possible for exploration and analysis. The homogeneity of the sample will be analyzed and normality tests will be performed.

The results are evaluated by comparing the differences between the groups with mixed linear model and T-test statistics to test the hypothesis that the means of two groups are or are not significantly different from each other.

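### The stated total of 237 does not equal the sum of the stated arms (118 + 117 = 235), so the recruitment target is ambiguous by two patients

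*Protocol article*

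**What the plan says.** The only sample size statement is one sentence in section 2.1 (Patients) of the protocol article. It opens with the total, "A sample size of (*n* = 237", and continues with the split, "with a proportional distribution for each arm of the study (group TR = 118 + control group = 117". It closes "with an expected proportion of losses (R = 15%) and a confidence index IC = 95% was used".

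The same section then describes how collaborating hospitals will help to reach the target size. Section 2.2 (Randomization and Single Blinding) has the allocation sequence generated before patients are included. Neither section repeats or corrects the numbers.

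**The concern.** A total and its arms should add up exactly. Here three figures stand in one sentence and at least one of them is wrong. The article describes two groups only, with no third arm or reserve group that could hold two more patients. The figures are in use: recruitment aims at the total, and an allocation list prepared in advance needs a known length. Later reports will also compare the number enrolled with the number planned, and a reader would not know which planned number applies.

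A smaller matter is that the sentence names a confidence level and a loss rate but no outcome, margin or effect, SD or power. The reader therefore cannot recompute the size to find out which of the two totals was intended.

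**Working it through.** **Inputs from the article (section 2.1).** Total 237; telerehabilitation arm 118; control arm 117; expected losses 15%; confidence 95%.

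**Step 1: the sum.** 118 + 117 = 235, and 237 − 235 = 2. As a share of the total, 2 / 237 = 0.8%.

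**Step 2: can the loss allowance show which total was meant?** Inflating a number of completers n by n / (1 − 0.15):

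- 201 / 0.85 = 236.5, which rounds up to 237.
- 199 / 0.85 = 234.1, which rounds up to 235.

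Both totals are possible inflated sizes. The simpler inflation n × 1.15 does not separate them either: 206 × 1.15 = 236.9 and 204 × 1.15 = 234.6. The loss rate does not settle the question.

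**Step 3: evaluable patients under each total.**

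- 0.85 × 235 = 199.75, or 99.9 per arm.
- 0.85 × 237 = 201.45, or 100.7 per arm.

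**Step 4: effect of the gap on power.** The article gives no effect or margin, so 0.40 SD is assumed for illustration. For a two-sample t-test at two-sided 5%, with the per-arm numbers from step 3:

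| Planned total | Evaluable per arm | Power at 0.40 SD |
|---|---|---|
| 235 | 99.9 | 80.3% |
| 237 | 100.7 | 80.6% |

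The difference is about 0.3 percentage points.

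**Step 5: what about 100 per arm corresponds to.** With 100 and 99 completers, the two-sample t calculation gives a detectable difference or margin of 0.399 SD at 80% power and 0.462 SD at 90% power. This holds for two-sided 5%, or for one-sided 2.5% with a true difference of 0, without covariate adjustment.

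**Step 6: why the two stated inputs do not fix the size.** At a 5% level with 15% losses, the required total depends on values that are not in the sentence. For a comparison of two means (normal approximation), assumed effects of 0.2 to 0.5 SD, 80% or 90% power and one- or two-sided testing give totals from 118 (0.5 SD, one-sided 5%, 80%) to 1238 (0.2 SD, two-sided 5%, 90%). Totals near the stated ones also occur: 238 for 0.35 SD, one-sided 5%, 80% power, and 233 for 0.40 SD, two-sided 5%, 80% power. All of these effects and powers are assumptions. They show the range and do not reconstruct the authors' calculation.

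**The case against.** The strongest reply is that two patients in 237 change nothing of substance. As to consequence, that stands: no analysis or conclusion turns on it, and power moves by about 0.3 points. It does not remove the error. The figures contradict each other within one sentence, and condensing a full protocol into an article does not explain that.

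A reader might go further and infer that the sample size is unsupported, because only 95% confidence and 15% losses are named while the hypothesis in the Introduction is that telerehabilitation "presents no inferior results in the improvement of functional capacity and quality of life compared to those obtained with a health education program". The documents do not carry that reading. The sentence does not say that these were the only inputs. Margin, SD and power are details that an article commonly leaves to the full protocol, which is not at hand. The size cannot be verified here, but it is not shown to be wrong, too small or too large.

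Nor can it be said that no ordinary calculation reaches the stated figures. With a t-test, 0.40 SD at 80% power and two-sided 5% needs 99.1, so 100 per arm, and 200 / 0.85 = 235.3, close to the sum of the printed arms. This does not prove what was done, since 0.40 SD appears nowhere in the article.

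**Conclusion.** The mismatch stands and is minor. The article gives 237 for arms that add to 235, and nothing else in it says which is right. The target and the allocation list are ambiguous by two patients, or 0.8%.

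The negligible effect on power rests on the stated 15% losses, near-equal arms, an assumed 0.40 SD and an unadjusted t-test. It also counts lost patients as contributing nothing. The planned mixed model could use the 4-week measure of a patient lost later, so about 100 per arm is, if anything, a cautious count.

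The 0.40 SD and 0.46 SD figures illustrate what about 100 per arm corresponds to. They are not a basis for choosing a margin, which has to be justified on clinical grounds and not fitted to the sample. The article also places several measures (STS, SPPB, SF-12 and EQ-5D) under its main variable, so these figures cannot be tied to one primary outcome.

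**What to change.** Go back to the original calculation, find the intended number, and correct the sentence in section 2.1 so that total and arms agree: either 235 = 118 + 117, or 237 = 119 + 118. Check that the allocation list has the same length. The correction by itself gives no reason to enrol beyond the intended target.

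While the sentence is open, report what was actually used: the outcome, the margin or effect, the SD, the power and whether the test was one- or two-sided. If those inputs are in the full protocol, a cross-reference is enough.

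The cost is one corrected sentence and a check of the allocation list. The design and the analysis do not change.

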### 2.2. Randomization and Single Blinding

Before patient inclusion, a research secretary will generate the allocation sequence and randomly assign patients consecutively with opaque sealed numbered envelopes. A computerized random number generator will be used. The research secretary will be instructed not to reveal the allocation sequence to any of the research team. The nature of the intervention in both groups does not allow blinding of patients and physiotherapists. It is therefore a single-blind study, where the evaluator does not know the nature of the intervention.

Study subjects are randomly assigned to either the TR group or the control group through a computerized randomization system. Subjects receive an initial evaluation based on clinical parameters and follow-up discharge reports. Data will be collected by an evaluator and integrated into research databases.

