### 2.4. Outcome Measures

The initial assessment includes a self-made clinical interview for anamnesis conducted via videoconference.

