#### 2.4.3. Secondary Explanatory Variable 

##### Satisfaction and Usability

The acceptance and usability of telemedicine applications is a prerequisite for identifying the potential clinical benefits of this technology. It is therefore important to complement this research with tools that examine patient satisfaction and perception [40]. An adaptation of the Telemedicine Satisfaction and Usefulness Questionnaire (TSUQ), whose psychometric analysis supports construct validity and internal consistency reliability and which is available in English and Spanish will be used [40]. The instrument used showed high reliability (Cronbach’s alpha 0.8) and evidence of validity with respect to perception in telemedicine [41]. Includes 17 questions that are assessed with a 5-point Likert subjective scale (1 totally disagree and 5 completely agree). The individual obtains scores from 17 to 85. The higher the score, the better the perception of the telerehabilitation intervention. Therefore each of the scores of the 17 variables indicated and finally the total score of the Test will be analyzed [40,41].

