### 2.5. Data Collection Procedure and Statistical Analysis

Once the study subjects have been informed, data will be collected for statistical analysis. The procedure to register different outcomes will be performed at baseline T.0 (Pre), at 4 weeks after the start of the intervention T.1 (Post1), and 8 weeks when the intervention ends T.2 (Post). Schedule of enrollment, interventions, and assessments is shown in Table 1. Initial evaluation (Pre) and measures at four and eight weeks (Post 1 and Post 2) will be carried out by an evaluator at the headquarters designated for this purpose, facilitating the access of the patient and after confirmation of the appointment by the research secretary or by means of telecommunication tools that allow the realization of the different measuring instruments.

The data will be added to the database created for this purpose and managed by the principal researcher using exportable data tables for statistical analysis. Each of the participating subjects will be assigned a study participation number, and the results of each of the variables analyzed will be collected. The principal investigator will be in charge of the anonymization of the data, so that the data will be recorded by eliminating the link with the identifiable person.

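### As written, the only blinded person, the evaluator, can learn the arm from the week-4 telerehabilitation satisfaction questionnaire before the week-8 STS and SPPB, and no rule fixes assessment mode

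*Protocol article*

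**What the plan says.** All references are to the protocol article.

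- **Who is blinded.** Section 2.2 states that "The nature of the intervention in both groups does not allow blinding of patients and physiotherapists" and concludes: "It is therefore a single-blind study, where the evaluator does not know the nature of the intervention". No other role is said to be blinded.
- **Who collects.** Section 2.2 adds: "Data will be collected by an evaluator and integrated into research databases". Section 2.5 says: "Initial evaluation (Pre) and measures at four and eight weeks (Post 1 and Post 2) will be carried out by an evaluator at the headquarters". No instrument is excepted and no second collector is named.
- **What is collected at week 4.** In Table 1 the TSUQ and the direct costs are marked at T.1, T.2 and close out. STS, SPPB, SF-12 and EQ-5D are marked at the same points and at T0.
- **What the TSUQ measures.** Under Satisfaction and Usability: "The higher the score, the better the perception of the telerehabilitation intervention".
- **How assessments are done.** Section 2.5 offers attendance at the headquarters "or by means of telecommunication tools that allow the realization of the different measuring instruments". It gives no rule for choosing between the two.

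**The concern.** Patients and physiotherapists know the treatment, so the evaluator's ignorance of it is the only blinding safeguard that the article claims. STS and SPPB depend on how the tester encourages, counts and times. A tester who knows the arm can shift them without meaning to.

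A control patient has no telerehabilitation to rate. Whoever hands over or reads out the TSUQ therefore has a strong clue to the arm. If that is the evaluator at week 4, the week-8 STS and SPPB are no longer protected. If the TSUQ comes before the functional tests at the week-4 visit, those tests are exposed as well.

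The open choice of assessment mode is a second, separate risk. A timed 4-metre walk, balance stands and a supervised STS may not give the same result at a designated site as in a home over video. If mode changed between visits, or came to differ between arms, that difference would enter the comparison. The hypothesis is that telerehabilitation is not inferior, so a shift in its favour could yield a false success, and a shift the other way could hide a true one.

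**Working it through.** The article gives no figure on this point to reproduce. The check is a cross-reading, followed by an illustration of scale.

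**1. TSUQ route**

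| Step | Source | Content |
|---|---|---|
| a | Section 2.2 | Only the evaluator is stated to be blinded |
| b | Sections 2.2 and 2.5 | An evaluator collects the data and carries out the week-4 and week-8 measures, none excepted |
| c | Table 1 | TSUQ is among the week-4 assessments, with STS and SPPB |
| d | Satisfaction and Usability | The TSUQ score rates telerehabilitation |
| e | Table 1 | STS and SPPB are repeated at week 8 |

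From b, c and d, the evaluator can learn the arm at week 4. With e, this happens before the week-8 tests. It contradicts a unless some shielding step exists, and the article describes none.

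**2. Session-count route**

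Table 1 also marks direct costs at week 4, and the cost-effectiveness section derives them from session counts in both groups. Neither that section nor Section 2.3, which has adherence deviations logged daily, names the person who records them. This route is possible, no more.

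**3. Assessment mode**

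Section 2.5 permits both modes. Nothing links the mode to a patient, a visit or an arm, and nothing holds it constant. Variation by visit or by arm is permitted but not stated to occur.

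**4. Scale, by assumption only**

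- Evaluable patients: 118 × 0.85 = 100.3 and 117 × 0.85 = 99.5, so about 100 per arm (arm sizes and 15% loss from Section 2.1).
- SE of the difference in SD units: √(2/100) = 0.141.
- Let b be an average shift in favour of telerehabilitation. With the true difference exactly at the non-inferiority limit, the false-success rate at one-sided 2.5% is 1 − Φ(1.96 − b/SE), whatever the limit is.

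| Assumed b (SD) | b/SE | False-success rate |
|---|---|---|
| 0 | 0 | 2.5% |
| 0.1 | 0.71 | 10.5% |
| 0.2 | 1.41 | 29.3% |

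Here b is an average over the whole comparison. If a 0.2 SD shift affected only half of one arm, b would be 0.5 × 0.2 = 0.1. The article gives no value for b, so the table shows sensitivity to bias and does not estimate it.

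**The case against.** The best reply is that an article need not say who hands out a questionnaire or in what order. The TSUQ is a 17-item rating scale that a patient could fill in unseen, and Section 2.1 requires every patient to have reliable e-mail or WhatsApp. The article also does not say that only telerehabilitation patients receive it. The full protocol, which is not shown, may contain a shielding step.

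This shows that unblinding is not certain, and that part stands. It does not remove the point, because the article is not merely silent: it assigns the week-4 measures to an evaluator without exception and puts the TSUQ among them. Giving the TSUQ to everyone would not help either if the evaluator saw or heard the answers.

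Four stronger readings are tempting, and the article does not support them:

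- **The evaluator collects session counts.** A mark in Table 1 dates the variable. It does not say who records it.
- **Mode follows arm.** One might expect remote testing for telerehabilitation patients and in-person testing for controls. But Section 2.1 requires home internet of all patients, and Section 2.4 describes a "self-made clinical interview for anamnesis conducted via videoconference" with no distinction by arm. Some controls are confined at home under Section 2.3, and the assessment headquarters is not said to be the controls' rehabilitation centre.
- **The error rates describe this trial.** They are correct arithmetic on an assumed bias.
- **All main outcomes are affected.** SF-12 and EQ-5D are reported by unblinded patients, so evaluator blinding does not protect them in any case.

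**Conclusion.** The concern holds in a limited form. Followed as written, the plan can disclose the arm to its only blinded person at week 4, before the week-8 STS and SPPB. It also leaves the assessment mode free to vary by visit or by arm.

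The TSUQ part rests on a plain reading of Sections 2.2 and 2.5 with Table 1, and on the assumption that no unstated step keeps the questionnaire from the evaluator. The session-count route is only possible, and a mode difference between arms is a risk left open. The size of any bias cannot be derived from the article; the illustration shows only that a modest average shift would matter at about 100 patients per arm. The point is confined to STS and SPPB. It is worth correcting because the remedy costs little, but it does not show that the blinding has failed or will fail.

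**What to change.** 1. **TSUQ.** Have telerehabilitation patients complete it themselves, for example on an online or e-mailed form, with the answers kept from the evaluator. Alternatively, give it only after the week-8 functional tests, which forgoes the week-4 reading.
2. **Session counts.** Take them from existing records that are not shown to the evaluator.
3. **Assessment mode.** Choose each patient's mode before allocation and keep it for T0, T.1 and T.2 where feasible. Record the mode actually used at each visit and examine it in a sensitivity analysis of STS and SPPB.
4. **Disclosure.** Ask patients not to mention their treatment to the evaluator.

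**Cost.** Some wording in the visit procedures, one data field per visit and one sensitivity analysis; no extra staff. Visit mode becomes slightly less flexible, and some switches may be unavoidable, for example when a patient is confined. That is why the mode used should be recorded as well as planned. If the evaluator is already shielded from the TSUQ, one sentence saying so settles that part.
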